# The impact of the time of drug administration on the effectiveness of combined treatment of hypercholesterolemia with Rosuvastatin and Ezetimibe (RosEze): study protocol for a randomized controlled trial

**DOI:** 10.1186/s13063-017-2047-8

**Published:** 2017-07-11

**Keywords:** Adherence, Cardiovascular risk, Coronary artery disease, Dyslipidemia, Ezetimibe, Hydroxymethylglutaryl-CoA, Hypercholesterolemia, Morning/evening dosing, LDL-C, Rosuvastatin

## Abstract

**Background:**

Hypercholesterolemia is one of the main risk factors for cardiovascular disease. The first line treatment for hypercholesterolemia is statin therapy. When the expected low-density lipoprotein cholesterol (LDL-C) concentration is not achieved, the pharmacotherapy may be extended by combining the statin with the cholesterol absorption inhibitor ezetimibe.

**Methods/design:**

The study is designed as a randomized, open-label, single-center, crossover study evaluating the effectiveness of combined therapy with rosuvastatin and ezetimibe for hypercholesterolemia. The study is planned to include 200 patients with hypercholesterolemia ineffectively treated with statins for at least 6 weeks. After enrollment participants are randomized into one of two arms receiving rosuvastatin and ezetimibe. In the first arm the study drug is administered in the morning (8:00 am) for 6 weeks and then in the evening for the next 6 weeks; in the second arm the study drug is administered at first in the evening (8:00 pm) for the first 6 weeks and then in the morning for the following 6 weeks. In order to minimize non-adherence to the treatment, all patients will receive the study drug free of charge. The primary outcome of the study is change in LDL-C at 6 and 12 weeks of the treatment, depending on the time of day of study drug administration. The secondary endpoints include change in total cholesterol, high-density lipoprotein (HDL) cholesterol, triglycerides, apolipoproteins ApoB and Apo AI, non-HDL cholesterol, small, dense (sd)-LDL cholesterol, lipoprotein(a), glucose, glycated hemoglobin, high-sensitivity C-reactive protein, aspartate aminotransferase, alanine aminotransferase, gamma-glutamyl transferase, and creatine kinase at 6 and 12 weeks of the study drug treatment, as well as assessment of plasma fluorescence using stationary and time-resolved fluorescence spectroscopy at baseline and at 6 and 12 weeks of the therapy.

**Discussion:**

The RosEze trial is expected to demonstrate whether there is a significant difference in the effectiveness of the lipid-lowering therapy in reducing the concentration of cholesterol when the medications are taken in the morning compared with the evening time of day.

**Trial registration:**

ClinicalTrials.gov, NCT02772640. Registered on 28 March 2016.

**Electronic supplementary material:**

The online version of this article (doi:10.1186/s13063-017-2047-8) contains supplementary material, which is available to authorized users.

## Background

Hypercholesterolemia is one of the main risk factors for cardiovascular disease (CVD) [1]. Despite enormous progress in the treatment of coronary artery disease (CAD), patients after surviving their first episode are at risk of recurrence [2]. Hypercholesterolemia is a modifiable risk factor for CVD. Lifestyle changes [3], increased daily physical activity [4–7], as well as optimized diet [8–12] may lead to normalization of specific cholesterol fractions. This strategy, however, often fails or is not sufficient, thus providing the need for pharmacotherapy. The current guidelines recommend statins as the first choice drugs for the treatment of hypercholesterolemia up to the highest recommended dose or the highest tolerable dose (class of recommendation I, level of evidence A) [2]. According to a meta-analysis of studies assessing statins, each 1.0 mmol/L (~40 mg/dL) reduction in low-density lipoprotein cholesterol (LDL-C) corresponds to a 10% reduction in all-cause mortality and a 20% reduction in the number of deaths from CAD [13]. Furthermore, each 1 mmol/L (40 mg/dL) reduction in LDL-C translates into a 23% and 17% reduction of the risk of major coronary events and stroke, respectively. Similar results concerning the efficacy and safety of lipid-lowering therapy using statins were obtained in meta-analyses of studies on primary prevention [14–16]. Statins are a heterogeneous group of drugs with respect to their LDL-C reduction power. So far, the most potent statin is rosuvastatin. However, despite intensive statin therapy, only a small group of patients (approximately 20%) reach the therapeutic lipid-lowering goal [17–20]. When the LDL-C goal is not achieved, the combination of statin with a cholesterol absorption inhibitor — ezetimibe — may be considered (class of recommendation IIa, level of evidence B) [2]. Statin dose titration seems to be less effective compared with the combined therapy with statin and ezetimibe [21]. The combination of statin with ezetimibe reduces the LDL-C by an additional 15–20% [22].

Unfortunately, despite a wealth of evidence on the efficacy and effectiveness of statins in both primary and secondary prevention, statin adherence remains a consistent barrier, with rates below 50% demonstrated in several studies [2, 23]. Adherence declines over the duration of treatment [2, 24–28], and this phenomenon is even more pronounced in patients treated for primary compared with secondary prevention of CVD [2]. It was demonstrated in a systematic review and meta-analysis that poor adherence is not limited to statins but to all medications used in secondary prevention for CVD [2, 29, 30]. Furthermore, non-adherence translates into increased healthcare costs of morbidity, hospital readmissions, and mortality [31–35]. There are many determinants of non-adherence to different medications including statins [36–38]. One of the reasons for non-adherence is a large number of drugs taken daily by the patient. Thus, more benefit is achieved with combined drugs containing statin and ezetimibe. Tablets comprising both of these drugs (statin and ezetimibe) simplify the drug administration and increase the probability of drug compliance. Furthermore, the use of these tablets may translate into increased probability for achieving therapeutic goals in hypercholesterolemia treatment [39]. Taking into account the metabolism of cholesterol and possible drug-drug interactions, it is recommended to administer simvastatin in the evening [40]. Rosuvastatin can be administered at any time of the day [41]. In our everyday practice we meet many patients with hypercholesterolemia treated with statins. All of them take the statin in the evening; whereas, for combined treatment with ezetimibe, they take the latter in the morning.

Until now there were no studies assessing the effectiveness of the combined treatment of hypercholesterolemia with rosuvastatin and ezetimibe according to the timing of the drug administration. To fill this evidence gap, the goals of this study are to determine whether the time of the day of rosuvastatin and ezetimibe administration plays any role in the effectiveness of the drug, and to identify side effects of combined therapy with rosuvastatin and ezetimibe administered at the same time of the day. Furthermore, we aim to assess whether administration of lipid-lowering drugs in the morning improves adherence compared with their evening administration.

Considering the potency of rosuvastatin, which is further enhanced when administered in combination with ezetimibe, we expect significant reduction of LDL-C concentration. However, the role of the time of drug administration in this case is questionable and worth further evaluation.

## Methods

The study is designed as a randomized, open-label, single-center, crossover study evaluating the effectiveness of combined therapy with rosuvastatin and ezetimibe for hypercholesterolemia. The study is conducted with full respect to regulations established in the Declaration of Helsinki. The eligibility criteria for enrollment into the study include adult patients with hypercholesterolemia defined according to the European guidelines [2] and ineffectiveness of statin monotherapy in the treatment of hypercholesterolemia after at least 6 weeks. All study participants will have been on statin therapy due to secondary prevention indications. Furthermore, they are eligible for the study when, despite statin monotherapy, the LDL-C concentration is higher than 70 mg/dL. Key exclusion criteria include the following: active liver disease; unexplained persistent increase in serum transaminase levels, including more than three times the upper limit of normal activity of one of them; severe renal impairment (creatinine clearance <30 mL/min); myopathy; concomitant treatment with cyclosporine and gemfibrozil; pregnancy or lactation; women of childbearing age not using effective methods of contraception; symptoms of muscle damage after using statins or fibrates in the past; activity of creatine kinase of more than five times the upper limit of normal.

The study is provided by the Department of Cardiology, Antoni Jurasz University Hospital No. 1 in Bydgoszcz, Poland.

After the enrollment, all participants are randomized into one of two arms receiving rosuvastatin and ezetimibe. The study drug (rosuvastatin with ezetimibe) is given: (1) in the morning (8:00 am) for 6 weeks and then in the evening for the next 6 weeks in the first arm; (2) in the evening (8:00 pm) for the first 6 weeks and then in the morning for the following 6 weeks in the second arm. In order to encourage adherence to the treatment, all patients will receive the study drug free of charge over the entire observational period. We plan to enroll 200 patients with ineffectively treated hypercholesterolemia. The scheme of the study and detailed plan of the study are presented in Figs. 1 and 2, respectively. The Standard Protocol Items: Recommendations for Interventional Trials (SPIRIT) checklist is provided as Additional file 1.

**Fig. 1 Fig1:**
[figure not shown]
Scheme of the trial

**Fig. 2 Fig2:**
[figure not shown]
Detailed plan of the study (SPIRIT figure)

### Endpoints

The primary outcome of the study is change in LDL cholesterol (LDL-C) at 6 (0 vs 6) and 12 (0 vs 12) weeks, as well as between the 6^th^ and 12th weeks, of study drug treatment (combination of ezetimibe and rosuvastatin), depending on the time of day of study drug administration.

The secondary endpoints include:Change in total cholesterol, high-density lipoprotein cholesterol (HDL-C), triglycerides (TGs), apolipoprotein B (ApoB), apoliprotein AI (Apo AI), non-HDL-cholesterol, small, dense-LDL-cholesterol (sd-LDL-cholesterol), lipoprotein(a) at 6 (0 vs 6) and 12 (0 vs 12) weeks, as well as between the 6th and 12th weeks of study drug treatment (combination of ezetimibe and rosuvastatin), depending on the time of day of study drug administrationAssessment of glucose metabolism parameters: glucose, glycated hemoglobin (HbA1c) at baseline and at 6 (0 vs 6) and 12 (0 vs 12) weeks, as well as between the 6th and 12th weeks of treatment with study drugAssessment of high-sensitivity C-reactive protein (hsCRP) at baseline and at 6 (0 vs 6) and 12 (0 vs 12) weeks, as well as between the 6th and 12th weeks of treatment with study drugAssessment of aspartate aminotransferase (AST), alanine aminotransferase (ALT), gamma-glutamyl transferase (GGT), and creatine kinase (CK) at baseline and at 6 (0 vs 6) and 12 (0 vs 12) weeks, as well as between the 6th and 12th weeks of treatment with study drugAssessment of plasma fluorescence using stationary and time-resolved fluorescence spectroscopy at baseline, at 6 (0 vs 6) and 12 (0 vs 12) weeks, as well as between the 6th and 12th weeks of treatment with study drug

Apart from the analysis in the whole population, the above-mentioned endpoints will be analyzed in subgroups depending on age, sex, and presence of other comorbidities.

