### The statistical analysis

Since there is no reference study examining the effectiveness of combined treatment of hypercholesterolemia with rosuvastatin and ezetimibe according to timing of drug administration, we decided to perform an internal pilot study of 20 patients to estimate the final sample size. The means and standard deviations of reduction in LDL-C were 53.25 ± 31.49 mg/dL and 57.71 ± 30.35 mg/dL during morning and evening administration, respectively. The correlation coefficient between total cholesterol reduction during morning and evening drug administration was 0.901. Based on these results and assuming a two-sided alpha value of 0.005, we calculated using the *t* test for dependent variables that enrollment of 157 patients would provide a 98% power to demonstrate a significant difference in total cholesterol level. To compensate for potential withdrawal of consent or loss of study participants due to other reasons, we plan to enroll 200 patients.

The statistical analysis will be carried out using the Statistica 12.0 package (StatSoft, Tulsa, OK, USA). Normal distribution of quantitative variables will be assessed with the Shapiro-Wilk test. Depending on the results of the Shapiro-Wilk test parametric, the Student *t* tests, the one-way analysis of variance (ANOVA) or a non-parametric test (the Mann-Whitney *U* test, Wilcoxon’s signed rank test, or the Kruskal-Wallis ANOVA, multiple comparison test) will be used. The χ^2^ test, the χ^2^ with the Yates correction, or Fisher’s exact test will be used for qualitative variables depending on subgroup size. To assess factors influencing plasma fluorescence parameters, correlation analysis and multiple regression analysis will be conducted. Two-sided differences will be considered significant at *p* < 0.05.

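### The primary outcome lists three LDL-C changes (0–6, 0–12 and 6–12 weeks) without saying which decides, although the trial is sized on one paired morning–evening contrast

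*Protocol article*

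**What the plan says.** **Protocol article, Endpoints.** The primary outcome opens with two changes from baseline, "The primary outcome of the study is change in LDL cholesterol (LDL-C) at 6 (0 vs 6) and 12 (0 vs 12) weeks", then adds a third, "as well as between the 6^th^ and 12th weeks, of study drug treatment", all qualified by "depending on the time of day of study drug administration". The section gives no order among the three, no rule for combining them, and no statement of which patients or periods are set against each other.

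**Abstract, Methods/design.** The shorter version reads "The primary outcome of the study is change in LDL-C at 6 and 12 weeks of the treatment", again by time of dosing. The week 6 to week 12 change is not mentioned.

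**Methods.** The design is a two-sequence crossover. The drug is taken "in the morning (8:00 am) for 6 weeks and then in the evening for the next 6 weeks in the first arm", and in the reverse order in the second arm. At each follow-up visit the two arms have therefore just finished opposite dosing times.

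**The statistical analysis.** The internal pilot gave LDL-C reductions of "53.25 ± 31.49 mg/dL and 57.71 ± 30.35 mg/dL during morning and evening administration". The size is justified with a "test for dependent variables that enrollment of 157 patients would provide a 98% power", at a two-sided alpha of 0.005, for a difference in total cholesterol. The analysis paragraph then lists Student t tests, one-way ANOVA, Mann-Whitney, Wilcoxon signed-rank and Kruskal-Wallis tests, chosen by a normality test, with significance at p < 0.05. None is tied to the primary outcome.

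**The concern.** The trial asks one question: does morning or evening dosing lower LDL-C more? A crossover answers it by comparing each patient with himself or herself, and the sample size relies on that. The primary outcome is instead written by visit, and the three changes it lists can be analysed in ways that differ greatly:

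- **Between arms.** The 0–6 change in one arm against the other is a parallel-group comparison. The 0–12 change is the same with dosing times reversed. Neither uses the within-patient correlation on which the sample size depends.
- **Within an arm.** The 0–6 and 0–12 changes then measure the combination against earlier statin monotherapy, which is not the question.
- **Regrouped by dosing time within patient.** The two changes become inputs to the one paired contrast.

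The listed tests include both paired and independent-group methods, so the analysis text does not settle the choice. At stake is whether the stated power belongs to the test that will be called primary. There could also be three primary p-values that disagree, in an open-label trial, with no stated rule for choosing among them.

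**Working it through.** **Inputs** (The statistical analysis): mean LDL-C reductions 53.25 (morning) and 57.71 (evening) mg/dL; SDs 31.49 and 30.35; 157 patients, 200 enrolled; alpha 0.005 in the sample-size text and 0.05 in the analysis text. The correlation is stated for total cholesterol: "The correlation coefficient between total cholesterol reduction during morning and evening drug administration was 0.901". It is borrowed here for LDL-C. Allocation is assumed 1:1, as no ratio is stated.

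**1. The plan's own power figure**
- Difference: 57.71 − 53.25 = 4.46 mg/dL.
- SD of the paired difference: √(31.49² + 30.35² − 2 × 0.901 × 31.49 × 30.35) = √190.5 = 13.80.
- Standardised effect: 4.46 / 13.80 = 0.323. Noncentrality with 157 patients: 0.323 × √157 = 4.05.
- Paired t test, two-sided 0.05: power 98.0%, and 157 is the smallest number that reaches 98%.
- Two-sided 0.005, as stated: power 88.3%. Reaching 98% would take 231 patients.

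The 98% therefore belongs to the paired contrast at 0.05. It also depends on the borrowed correlation. At 0.80 the SD of the difference is 19.59 and power at 0.05 is 81%; at 0.85 they are 16.97 and 91%.

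**2. Regrouping by dosing time within patient**

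Let B, L6 and L12 be LDL-C at baseline, week 6 and week 12.
- Morning-first arm: evening minus morning reduction = (B − L12) − (B − L6) = L6 − L12.
- Evening-first arm: evening minus morning reduction = (B − L6) − (B − L12) = L12 − L6.

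The baseline cancels. The regrouped 0–6 and 0–12 changes and the 6–12 change, signed by sequence, are the same quantity. On this reading there is one test with the power in step 1. Comparing the 6–12 change between sequences, which removes a common period effect, gave 98.0% power at 0.05 in simulation with 157 patients.

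**3. Comparing 0–6 (or 0–12) between arms**
- Pooled SD: √((31.49² + 30.35²) / 2) = 30.93. Standardised effect: 4.46 / 30.93 = 0.144.
- 157 patients, 78.5 per arm: SE = 30.93 × √(2 / 78.5) = 4.94; 4.46 / 4.94 = 0.90; power at two-sided 0.05 = 14.6%.
- 200 patients, 100 per arm: SE = 4.37; ratio 1.02; power 17.4%.
- Needed per arm at 0.05: about 755 for 80% power, about 1,550 for 98%.

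**4. Testing all three at 0.05, any one counting as success**

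Under no effect of dosing time, the third statistic is the difference of the first two. In simulation with correlation 0.901, the chance of at least one p < 0.05 was 11.3% by normal statistics and 11.1% by two-sample t tests with 78 and 79 patients. For correlations from 0 to 0.95 it was 10.9% to 12.2%, so the borrowed correlation matters little here. Three independent tests would give 1 − 0.95³ = 14.3%.

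**The case against.** The strongest reply is that the between-arm reading is not in the text. The Endpoints section never says that arms are compared at each visit. The sample-size paragraph reports reductions by dosing time and uses a paired test, which suggests that the trialists do regroup the 0–6 and 0–12 changes by timing. On that reading there is one test, about 98% power at 0.05, and no multiplicity. This stands as a fair and perhaps the likeliest reading, and it is why the low-power and error figures can only be conditional. It does not close the point: Endpoints lists the three changes separately, and the sample-size paragraph names total cholesterol as the powered variable.

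A reader might infer that the primary analysis has about 15% power, or that the trial's false-positive rate is more than double its nominal level. The documents support neither as a plain statement. The first needs a between-arm comparison. The second needs three separate tests and a rule that any one suffices. The 0.05 in the analysis text is a general threshold, not a decision rule for each time point. If all three had to be significant, the error could not exceed 5%, although power could then be no better than that of the weakest test.

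A reader might also take the abstract to contradict Endpoints. Its omission of the 6–12 change is largely condensation.

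Finally, multiplicity methods and test assignment may properly sit in an analysis plan that is not shown, and their absence is not the complaint. The definition of the primary outcome is stated in this document, and it does not match the contrast on which the trial was sized.

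**Conclusion.** The point holds as a badly fixed primary endpoint that should be corrected, not as a demonstrated failure of power or error control. Three visit-based changes share primary status with none decisive, while one paired contrast carries the sample size. The consequence depends on the reading:

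| Reading | Result at two-sided 0.05 |
|---|---|
| 0–6 and 0–12 regrouped by timing within patient | One test; 98% power with 157 patients (88% at alpha 0.005) |
| 0–6 or 0–12 compared between arms | About 15% power each with 157 patients, 17% with 200 |
| All three tested, any one counts | About 11% false positives |

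These figures rest on the pilot means and SDs, 1:1 allocation and 157 evaluable patients unless 200 is stated. The paired power also rests on the total-cholesterol correlation holding for LDL-C. The conflict between alpha 0.005 and 0.05 is a separate inconsistency, but it determines which paired power applies.

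**What to change.** Define one primary endpoint: the within-patient difference in LDL-C between the end of the 6-week morning period and the end of the 6-week evening period, both sequences combined and adjusted for period, tested once at two-sided 0.05. Make the 0–6 and 0–12 changes secondary or descriptive.

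Then bring the abstract, Endpoints and sample-size text into line with that definition. The sample-size text should name LDL-C instead of total cholesterol, use the LDL-C correlation from the pilot, and state the same alpha as the analysis.

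The cost is wording only: no extra patients, visits or blood samples, since LDL-C at weeks 6 and 12 is already measured. The article reports that recruitment is still under way, so the change can be made before analysis. The one downside is that the 0–6 and 0–12 changes lose primary status.

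### If the 0–6 and 0–12 week LDL-C changes are compared between arms, the listed tests leave the measured baseline unused: a modest, free precision loss, not a bias

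*Protocol article*

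**What the plan says.** The Methods section describes a "randomized, open-label, single-center, crossover study". One arm takes the drug in the morning and then in the evening; the other takes it "in the evening (8:00 pm) for the first 6 weeks and then in the morning for the following 6 weeks in the second arm".

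The Endpoints section gives the primary outcome, by dosing time, as "change in LDL cholesterol (LDL-C) at 6 (0 vs 6) and 12 (0 vs 12) weeks". The same sentence adds a third contrast, the change from week 6 to week 12. The secondary lipid endpoints use the same three time contrasts.

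The statistical analysis section sizes the trial on a t test for dependent variables. It then gives a general list for quantitative variables, chosen by a normality test: Student t tests, "the one-way analysis of variance (ANOVA) or a non-parametric test" (Mann-Whitney, Wilcoxon signed rank or Kruskal-Wallis). The list is not tied to endpoints or contrasts. Multiple regression is named only for plasma fluorescence. Under the section on blood sample collection, blood is drawn at enrolment and after 6 and 12 weeks, so a baseline LDL-C exists for every patient.

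**The concern.** At week 6 the first arm has been on morning dosing and the second on evening dosing; at week 12 this is reversed. A 0–6 or 0–12 week change compared by time of day at that visit is therefore a comparison of independent patients. Because the 6–12 week change is listed separately, a reader can fairly take the other two as comparisons in their own right.

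An unpaired test on the change carries the full between-patient spread, including the part that baseline predicts. The estimates would be less precise than the same data allow, and they would stand under a primary label beside a far more precise paired result. The secondary lipids at these visits are in the same position.

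**Working it through.** **Inputs.** From the statistical analysis section: pilot LDL-C reductions of "53.25 ± 31.49 mg/dL and 57.71 ± 30.35 mg/dL during morning and evening administration"; "The correlation coefficient between total cholesterol reduction during morning and evening drug administration was 0.901"; 157 patients for 98% power, "assuming a two-sided alpha value of 0.005"; 200 to be enrolled. The analysis level is two-sided 0.05. Not in the article, hence assumed: the correlation of baseline with follow-up or with change, and the ratio of their SDs.

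**1. The plan's own figure (paired test).**
- Difference: 57.71 − 53.25 = 4.46 mg/dL.
- SD of the paired difference: √(31.49² + 30.35² − 2 × 0.901 × 31.49 × 30.35) = 13.80. This borrows the correlation labelled total cholesterol.
- Standardized difference: 4.46 / 13.80 = 0.323.
- By the noncentral t, 157 patients give 88.3% power at two-sided 0.005, and 98% needs 231. At two-sided 0.05, power is 98.05% and 157 is exactly the number needed.

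The stated 157 and 98% thus belong to a paired test at 0.05. The mismatch in alpha and the total cholesterol label are separate matters. What counts here is that the sample size supports the within-patient contrast.

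**2. Baseline in the paired contrast.** (baseline − evening) − (baseline − morning) = morning − evening. Baseline cancels, so adjustment gains nothing.

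**3. Between-arm contrast, unadjusted.**
- Pooled SD of change: √((31.49² + 30.35²) / 2) = 30.93. This takes the pilot SDs as applying at each visit.
- SE with 100 per arm: 30.93 × √(2/100) = 4.37 mg/dL.
- Power for 4.46 mg/dL at two-sided 0.05: 17.4% with 200 patients, 14.5% with 157.

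**4. Between-arm contrast, adjusted for baseline, 100 per arm.** With equal SDs and baseline to follow-up correlation ρ, the change score has variance 2σ²(1 − ρ) and ANCOVA has σ²(1 − ρ²), a ratio of (1 + ρ)/2. More generally, with baseline-to-change correlation r, the ratio is 1 − r².

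| Assumption | Variance ratio | SE (mg/dL) | Power | Effective sample size |
|---|---|---|---|---|
| Unadjusted | 1 | 4.37 | 17% | 1 |
| Equal SDs, ρ = 0.8 | 0.90 | 4.15 | 19% | 1.1 × |
| Equal SDs, ρ = 0.5 | 0.75 | 3.79 | 22% | 1.3 × |
| Equal SDs, ρ = 0.3 | 0.65 | 3.53 | 24% | 1.5 × |
| r = 0.7 | 0.51 | 3.12 | 30% | 2.0 × |
| r = 0.8 | 0.36 | 2.62 | 39% | 2.8 × |

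The last two rows need treatment to narrow the spread of LDL-C. If k is the ratio of follow-up SD to baseline SD, r = (1 − kρ) / √(1 + k² − 2kρ). With ρ = 0.3, k = 0.8 gives 0.76 / √1.16 = 0.71, and k = 0.7 gives 0.79 / √1.07 = 0.76. A value of 0.8 needs a still smaller k.

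**5. Scale against the paired contrast.** With 157 patients the SE is 13.80 / √157 = 1.10 paired and 30.93 × √(2/78.5) = 4.94 between arms. Baseline would have to explain 1 − (1.10/4.94)² ≈ 95% of the change-score variance for the between-arm analysis to match.

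**The case against.** The strongest reply is that the article never says the primary comparison is an unpaired test of raw change. The Endpoints section names no test. The only test tied to the morning–evening comparison is the paired one, and a patient's 0–6 and 0–12 week changes can be read as the two halves of that pair. The unpaired tests on the list could be meant for other uses, such as the planned subgroup analyses. Covariates are also commonly set in an analysis plan, and none is shown.

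Most of this stands. A reader might infer that the trial's main comparison is between arms and wastes the baseline, or that its result would be biased. The documents do not support either inference: the powered contrast is within patient, baseline drops out of it, and in a randomized comparison an unadjusted change score is unbiased, with a standard error that already allows for chance baseline imbalance.

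What the reply does not remove is narrower. The three time contrasts are listed as separate parts of the primary outcome, two of them are between-arm when taken visit by visit, and the methods that are named for quantitative variables include independent-group tests but no baseline-adjusted model. The point concerns methods stated without being assigned, more than a missing detail.

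**Conclusion.** The point holds as a free precision improvement to contrasts that the sample size does not support. It is not an error in the main comparison.

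With 200 patients, the gain for a between-arm 0–6 or 0–12 week comparison is about 1.1 to 2.8 times the effective sample size, and power for 4.46 mg/dL rises from about 17% to between 19% and 39%. The lower part of that range (up to 24%) rests on equal SDs and ρ from 0.3 to 0.8; the upper part (30% to 39%) needs a narrower spread on treatment, which the article does not report.

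A reader might also infer that ANCOVA would make these comparisons adequate. It would not: on every assumption tabulated, power stays below 40%, and far more is lost by giving up the pairing than by ignoring baseline.

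**What to change.** Add two statements to the statistical analysis section.

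1. The within-patient morning–evening contrast in LDL-C is the main comparison and the one the sample size supports.
2. Any between-arm comparison of 0–6 or 0–12 week change in LDL-C or a secondary lipid uses ANCOVA: the value at that visit (or its change) on randomized arm, with the baseline value of the same marker as covariate, in place of an unpaired t test or Mann-Whitney test on change.

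If no between-arm comparison at weeks 6 and 12 is intended, the Endpoints section should say that these two changes enter only through the paired contrast, and the second statement is then unnecessary.

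The cost is two sentences. Baseline blood is already drawn from every patient, so no extra measurement, visit or patient is needed.

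### The primary outcome is three LDL-C contrasts with none named decisive, and one p < 0.05 rule covers these and every secondary and subgroup analysis

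*Protocol article*

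**What the plan says.** In the protocol article, section Endpoints, the primary outcome is the change in LDL-C from baseline to week 6, from baseline to week 12, and from week 6 to week 12, according to time of dosing. None of the three is singled out. The same three comparisons are listed for the secondary variables: eight other lipid and apolipoprotein measures, glucose, HbA1c, hsCRP, AST, ALT, GGT, CK and plasma fluorescence. The section ends by stating that, besides the whole population, "the above-mentioned endpoints will be analyzed in subgroups depending on age, sex, and presence of other comorbidities". No age cut-point, list of comorbidities or exploratory label is given.

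The section The statistical analysis states one criterion for all of this: "Two-sided differences will be considered significant at *p* < 0.05". The only multiplicity wording is a multiple comparison test listed beside the Kruskal-Wallis ANOVA. That is a post-hoc procedure for one kind of test, not control across contrasts, endpoints or subgroups.

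The same section sizes the trial on a single paired comparison of morning with evening dosing, "assuming a two-sided alpha value of 0.005", and concludes that "enrollment of 157 patients would provide a 98% power to demonstrate a significant difference in total cholesterol level".

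**The concern.** The trial asks one question: does time of dosing change the LDL-C response? With three primary contrasts, no order among them and an unadjusted 0.05 rule, a significant result on any one could be reported as a positive primary result. The error rate of that claim is then not 5%. This follows from what the article states, not only from something it leaves out.

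The same rule extends to the secondary variables and the subgroups, so some results will meet the criterion by chance, with nothing in the text to mark them as weaker evidence than the primary result.

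The 0.005 in the sample-size paragraph might suggest that a stricter standard was meant. It has to be checked whether that figure protects the plan.

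**Working it through.** **1. The plan's own sample-size figure**

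Inputs, all from The statistical analysis:
- LDL-C reductions of "53.25 ± 31.49 mg/dL and 57.71 ± 30.35 mg/dL during morning and evening administration" respectively.
- Correlation 0.901. The article attaches it to total cholesterol; it is applied here to LDL-C, as the calculation seems to do.
- Paired t test, N = 157.

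Formulas and results:
- Difference = 57.71 − 53.25 = 4.46 mg/dL.
- SD of the difference = √(31.49² + 30.35² − 2 × 0.901 × 31.49 × 30.35) = √(991.62 + 921.12 − 1722.21) = √190.53 = 13.80.
- Standardised difference = 4.46 / 13.80 = 0.323.

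Power from the noncentral t distribution, with noncentrality 0.323 × √N:

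| Two-sided alpha | Power at N = 157 | Power at N = 200 | N for 98% power |
|---|---|---|---|
| 0.005 (as stated) | 88.3% | 95.7% | 231 |
| 0.05 | 98.05% | 99.5% | 157 |

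The pair of 157 patients and 98% power reproduces at 0.05 and not at 0.005. The 0.005 therefore looks like a misprint and cannot be read as a multiplicity allowance.

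**2. Error rate of the primary outcome**

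Assume time of day has no effect, and read each contrast as a comparison by time of dosing, so that all three are null.
- If independent: 1 − 0.95³ = 14.3%.
- They are not independent, since the week 6 to 12 change equals the 0 to 12 change minus the 0 to 6 change. With equal correlation among the three visits, the chance that at least one passes |z| > 1.96 is the chance that the studentized range of three means exceeds 1.96 × √2 = 2.77, which is 12.2%.
- If weeks 6 and 12 correlate at 0.9 and each correlates with baseline at 0.3 to 0.5 (assumed values), simulation gives about 11%.

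So the figure is about 12%, against a nominal 5%.

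**3. The wider grid**

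Minimum count, with fluorescence as one variable: 1 + 8 + 2 + 1 + 4 + 1 = 17 variables; 17 × 3 = 51 whole-population tests. If two levels are assumed for each of age, sex and comorbidity, six subgroups are added: 51 × 7 = 357 tests.

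If every null is true, the expected number of false positives is 51 × 0.05 = 2.6, or 357 × 0.05 = 17.9, whatever the correlation. The chance of at least one does depend on correlation. By simulation:

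| Between-endpoint correlation | 0 | 0.3 | 0.5 | 0.7 | 0.9 |
|---|---|---|---|---|---|
| 51 whole-population tests | 88% | 82% | 70% | 53% | 32% |
| All 357 tests | 100% | 99.95% | 99.4% | 96% | 81% |

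With all 51 independent, the figure would be 1 − 0.95⁵¹ = 92.7%.

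**4. Why separate subgroup p-values would mislead**

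Suppose two equal halves share the same true difference of 4.46 mg/dL. At N = 157 each half has 80.5% power at 0.05, so exactly one half is significant with probability 2 × 0.805 × 0.195 = 31%. At N = 200 the power per half is 89.2%, and the figure is 2 × 0.892 × 0.108 = 19%.

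An interaction test on the same halves, for a difference between them as large as 4.46 mg/dL, has standard error √(2 × 190.53 / (N/2)). That is 2.20 at N = 157 and 1.95 at N = 200, giving about 53% and 63% power (normal approximation).

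**The case against.** **The analysis plan may settle this.** The article condenses a fuller document. Confirmatory status of secondary endpoints, subgroup cut-points and interaction tests are commonly left to an analysis plan, and a 0.05 sentence is conventional. This stands for those details, whose absence is no fault. It does not cover the primary outcome: the article itself states three primary contrasts and one threshold, and any later adjustment would change that rule.

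**The inflation can be exaggerated.** A reader might infer that chance findings are close to certain in the main analysis. The documents do not support that. Figures above 90% for the whole population need independent and truly null tests. Yet non-HDL-C is calculated (Blood sample collection and laboratory measurements), the lipid measures are related, and one of each three contrasts is the difference of the other two. The article expects LDL-C to fall on treatment (Background), and several secondary items are not tied to time of dosing. If the baseline contrasts are read as on-treatment change, many are not null, and the expected counts above are upper figures. Near-certainty appears only with the subgroups added, and the six strata are an assumption. AST, ALT, GGT and CK also serve as safety measures, where familywise control is not usually sought.

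**The subgroup comparison is not specified.** A reader might also infer that subgroup claims will rest on setting one subgroup's p-value against another's. The article says only that the endpoints will be analysed in subgroups. It neither states that comparison nor rules it out, and promises no subgroup recommendation.

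**Conclusion.** The point holds for the primary outcome. Three contrasts with none decisive, under an unadjusted 0.05 rule, give about a 12% chance of a false primary claim (11% to 14% over the correlation structures tried). This assumes that time of day has no effect, that the contrasts are compared by time of dosing, and that any one of them could carry the claim. If the baseline contrasts are instead read as change on treatment, the 12% does not apply, but a significant fall from baseline would not answer the timing question, which is equally a reason to name one decisive contrast.

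For the secondary and subgroup analyses, several chance results are likely under the stated rule. No exact number can be defended. It is not established that subgroup conclusions will rest on an invalid comparison; the 31% and 19% figures show only why that route should be closed.

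The 0.005 planning alpha does not rescue the plan, since it gives 88.3% power at 157 patients and not 98%. The two alphas in one section contradict each other.

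**What to change.** - Name the within-patient morning-minus-evening LDL-C difference, the paired comparison on which the trial was sized, as the single confirmatory test at two-sided 0.05. On the plan's own inputs, power stays at 98.05% with 157 patients and 99.5% with 200. Keeping all three contrasts confirmatory with Bonferroni (0.05/3) would give 94.7% and 98.4% for the same paired effect.
- Report the other LDL-C contrasts, the secondary endpoints and the subgroups as supportive or exploratory, with estimates and 95% confidence intervals. No published contrast needs to be dropped.
- Base any statement that the time-of-day effect differs between subgroups on an interaction estimate with its interval, not on separate within-subgroup p-values.
- Reconcile the 0.005 used for planning with the 0.05 used for analysis.

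The cost is a documented change of wording while the trial is recruiting, with no extra patients or measurements. Fewer secondary and subgroup results can be called significant, and interaction tests will have limited power: about 53% to 63% even for a subgroup difference as large as the whole planned effect, so a null interaction will not show that the effect is uniform.
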